Current daily and non-daily tobacco smokers (cigarettes, cigarillos hand-rolled cigarettes, pipe, cigar, or hookah) will be further interviewed on their smoking behaviour, motivation to stop smoking [28], strength of urges to smoke [39], as well as on primary and secondary outcomes. At the end of this interview, patients will be informed about the purpose of the misinformation regarding the interview content according to the requirements of the ethics committee.

By assessing the above-mentioned primary and secondary outcomes immediately after GP consultation through a face-to-face interview, we aim to maximise response rates and minimise recall bias.

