### Outcomes

#### Primary outcome

The primary outcome is defined as the number of patients who report the receipt of brief stop-smoking advice during the last consultation with their GP, irrespective of the training method, out of the total number of patients who stated to be current tobacco smokers at the time of the consultation with their GP. These data will be collected prior to and following the training through personal interviews in all consecutive patients immediately following GP consultation.

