### Patients

#### Baseline measurements

Following the consultation with their GP, a researcher of the study team will immediately conduct the brief baseline interview (~ 10–15 min) with the study (see Additional files 1 and 2). At the beginning of the interview, all patients will be asked about their age, sex, level of education, employment status, and health-related quality of life (EQ-5D [36]).

Patients will then be asked whether they smoke tobacco (cigarettes, hand-rolled cigarettes, pipe, cigar, or hookah). Answer categories will be: (1) “Yes, I currently smoke on a daily” or (2) “on a non-daily basis”, (3) “No, but I used to smoke in the past”, (4) “No, I have never smoked daily or occasionally”.

Current smokers of tobacco products will be asked further details on their smoking behaviour: how long it has been since they had smoked their last cigarette, the average number of cigarettes (or, e.g., pipes, cigars) they smoke per day, week or month (for occasional smokers), on their motivation to stop smoking (German version of the Motivation to Stop Smoking Scale, MTSS [28]), and their strength of urges to smoke (German version of the Strength of Urges to Smoke Scale, SUTS) [39]. These variables represent important co-variates or confounders for the planned statistical analyses.

Subsequently, data on the primary outcome will be collected. Smoking patients will be asked whether their GP started a conversation on the patient’s smoking behaviour during the preceding consultation at the same day. If the answer is “yes”, these patients will be asked whether or not their GP provided brief advice to quit smoking according to either 5A or ABC during the preceding consultation. This is operationalised by whether the GP asked for the smoking status (A1: both 5A and ABC), urged the smoker to quit (A2: both 5A and ABC), asked for the patients’ motivation to quit smoking (A3: only 5A), provided evidence-based stop-smoking therapy (A4: both 5A and ABC) by recommending or prescribing either: individual or group behavioural support (S1), NRT (S2), varenicline or bupropion (S3); and arranged a follow-up appointment (A5: only 5A). Furthermore, recommendations of a combination of therapies will be asked (e.g., “my GP recommended or prescribed me individual or group behavioural support AND NRT).

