### Power and sample size

Based on recent data from a study of the German population [13], we assume that about 18% of smokers are currently receiving brief advice on smoking cessation during a consultation with their GP. Training in either the 5A or ABC method is assumed to have a clinically relevant effect if it increases these rates by at least 10% (corresponding to an odds ratio of 1.77) between pre- and post-training.

Calculation of the required sample size is based on the primary analysis and is intended to ensure that a significant time effect between pre- and post-training can be detected with a probability of 80%, taking into account the clustering of patients in GP practices. The following assumptions were made: (a) 48 GP practices will be recruited (six study cycles with 4 GPs receiving the 5A training and 4 GPs receiving the ABC training each cycle); (b) the delivery rate of brief cessation advice prior to the training is 18%; (c) these rates vary among practices with assumed ranges from 9 to 32% in 95% of the practices (corresponding to a standard deviation (SD) of 0.40 on the logit scale); (d) the chance of receiving stop-smoking advice increases on average from 18 to 23% (5A method) or 33% (ABC method) after a training; and (e) varies among practices after the training (between 12 and 40% (5A method) or between 18 and 52% (ABC method) in 95% of the practices (equivalent to a SD of 0.05 for the time effect on the logit scale).

A simulation study based on these assumptions showed that 16 patients (respectively 8 prior to and 8 following the training) per practice are needed to evaluate the primary outcome with a statistical power of at least 80%. A total of 42 patients per practice (21 before and 21 after training) are needed to yield the same power when analysing the interaction between the time and group variable (secondary outcomes S10), resulting in a total study sample size of 2016 patients (respectively 1008 prior to and 1008 following the training). The R-code of this simulation can be provided on request.

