#### Analyses of primary and secondary outcome measures

The primary endpoint is dichotomous: patient reported receipt of brief stop-smoking advice delivered by the GP during the preceding consultation (yes or no). Hence, analyses of the primary outcome will be conducted using logistic regression models. Data are structured hierarchically (in clusters = practices), with the patients located within the practices. Since differences in rates of delivery of smoking cessation advice are expected among the practices, mixed effect models will be used. For the primary analysis, the model contains a fixed effect for time (dichotomous: pre- versus post training) and random effects for the practices and the time effect. This model will be adjusted for potential confounders measured at baseline: age, sex, SES, motivation to stop smoking, and strength of urges to smoke of the patients.

The same model will be applied to the secondary outcomes S1-S3 (recommendation of behavioural treatment, NRT, or medication), S4-S6 (patient-reported quit attempts at 4, 12, and 26 weeks following the consultation with the GP), and S7-S9 (patient-reported abstinence at 4, 12, and 26 weeks following the consultation with the GP).

In order to analyse differences between the 5A and ABC training (secondary outcome S10), the group variable (dichotomous: 5A or ABC training) and its interaction with time will be added to the models as fixed effects. In both models, the time effect and the interaction will be analysed by means of Wald tests (level of significance .05).

All participating patients will be included in an intention-to-treat analysis. The risk for missing data on the primary outcome and secondary outcomes S1-S3 will be relatively small, as these data will be collected though personal interviews. However, missing data will be imputed and recoded as patient-reported “no advice-to quit delivered by GP” (primary outcome) and “no treatment recommended or delivered by GP” (S1-S3). To examine the sensitivity of the results, a complete case analysis will be performed additionally, which means that all cases with missing data on the primary outcome will be excluded from the analysis. Missing data on secondary outcomes S4-S6 will be imputed and recoded as “no quit attempt”. Missing data on secondary outcomes S7-S9 will be imputed and recoded as “smoker” at follow-up.

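### Amount smoked is named as a covariate or confounder for the analyses, but the fixed adjustment list omits it; the pre-post effect is left slightly exposed to a change in smoker mix

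*Protocol article*

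**What the plan says.** The Baseline measurements section of the protocol article has every patient report whether they smoke daily, non-daily, formerly or never. The next paragraph lists further items for current smokers: time since the last cigarette, "the average number of cigarettes (or, e.g., pipes, cigars) they smoke per day, week or month (for occasional smokers"), motivation to stop, and strength of urges. It closes: "These variables represent important co-variates or confounders for the planned statistical analyses".

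The section on analyses of primary and secondary outcomes specifies the primary model: "the model contains a fixed effect for time (dichotomous: pre- versus post training) and random effects for the practices and the time effect". It then fixes the covariates: "This model will be adjusted for potential confounders measured at baseline: age, sex, SES, motivation to stop smoking, and strength of urges to smoke". For the remaining outcomes it states: "The same model will be applied to the secondary outcomes S1-S3", and it extends this to S4-S6 and S7-S9.

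The sample is described as "Current daily and non-daily tobacco smokers", interviewed "through personal interviews in all consecutive patients immediately following GP consultation", "resulting in a total study sample size of 2016 patients (respectively 1008 prior to and 1008 following the training"). Under Descriptive statistics, smoking characteristics are to be shown for the whole group and by study arm; a display by period (pre versus post) is not mentioned.

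**The concern.** Two sections of one document disagree on the covariates. One names four smoking measures as important for the analyses; the other keeps two of them and gives no reason for leaving out the rest. This is not detail deferred to an analysis plan, because the covariate list is written out.

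The design gives the omission some weight. The randomisation allocates GPs to 5A or ABC; it does not balance patients seen before training against patients seen after. The primary effect is a pre-post contrast pooled over both methods, without an untrained concurrent group, so covariate adjustment is a main protection against a change in who attends. If heavier or daily smokers are more likely to be advised, or less likely to be abstinent later, a change in their share between periods looks like an effect of training. Usual consumption describes behaviour before the visit, so adjusting for it does not risk removing an effect of the consultation that has just taken place.

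**Working it through.** **1. Side by side**

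| Measure | Named as covariate or confounder (Baseline measurements) | In the model |
|---|---|---|
| Motivation to stop | yes | yes |
| Strength of urges | yes | yes |
| Amount smoked | yes | no |
| Time since last cigarette | yes | no |
| Daily/non-daily status | no (recorded in the preceding paragraph) | no |

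**2. The plan's reference effect.** The article takes 18% before training and a relevant gain of 10 points. Odds ratio = (0.28/0.72)/(0.18/0.82) = 0.3889/0.2195 = 1.77, as stated.

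**3. A shift in mix with no training effect, unadjusted.** The documents give neither the share of daily smokers nor its relation to advice, so both are assumed. Daily status serves as a two-level stand-in for smoking intensity. Take a pre-training rate of 18%, a daily share moving from 75% to 85%, and an odds ratio of 2 for advice in daily versus non-daily smokers.

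- Let p be the advice rate in non-daily smokers; the daily rate is then 2p/(1+p).
- Solve 0.75 × 2p/(1+p) + 0.25p = 0.18. This gives p = 0.1126 and a daily rate of 0.2025.
- Post-training rate: 0.85 × 0.2025 + 0.15 × 0.1126 = 0.189.
- Spurious odds ratio: (0.189/0.811)/(0.18/0.82) = 1.06.

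With an odds ratio of 3 the same steps give a post-training rate of 0.193 and a spurious odds ratio of 1.09. Over advice odds ratios of 1.5 to 3 and shifts of 5 to 15 points, the spurious odds ratio is 1.02 to 1.14, which is 3% to 23% of ln 1.77.

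**4. After adjustment for an urge-type score.** The planned model keeps strength of urges, so step 3 overstates what remains. The 75% to 85% scenario was simulated with 400,000 patients per period and a score correlated with daily status. Practice effects and the other covariates were left out.

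| Correlation of score with daily status | Advice OR 2: score only | Advice OR 2: score + daily status | Advice OR 3: score only | Advice OR 3: score + daily status |
|---|---|---|---|---|
| 0 | 1.062 | 1.001 | 1.097 | 1.009 |
| 0.3 | 1.063 | 1.005 | 1.091 | 1.010 |
| 0.5 | 1.044 | 0.997 | 1.081 | 1.011 |
| 0.7 | 1.030 | 0.996 | 1.047 | 0.997 |

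Simulation error on the log scale is about √(1/(400,000 × 0.18 × 0.82) + 1/(400,000 × 0.19 × 0.81)) = 0.006. The residual is thus about 1.03 to 1.10, and adding daily status returns it to 1.00 to 1.01.

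**5. Scale.** ln 1.03/ln 1.77 = 0.030/0.571 = 5%; ln 1.10/ln 1.77 = 0.095/0.571 = 17%. The unclustered standard error of the log odds ratio with 1008 per period is √(1/(1008 × 0.18 × 0.82) + 1/(1008 × 0.189 × 0.811)) = 0.115, so the residual is about 0.3 to 0.8 of a standard error.

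**6. Could chance produce the shift?** The standard error of the difference in daily share is √(2 × 0.75 × 0.25/1008) = 0.019. A 10-point shift is about 5 standard errors, so it would need a systematic change in attendance.

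**7. Direction.** It can go either way. If non-daily smokers rise from 20% to 25% and advice reaches 10% of them and 20% of daily smokers, the rate moves from 0.20 × 0.10 + 0.80 × 0.20 = 18.0% to 0.25 × 0.10 + 0.75 × 0.20 = 17.5%, an unadjusted odds ratio of 0.97. For abstinence, with assumed rates of 25% and 7%, the same shift moves 10.6% to 11.5%, an unadjusted odds ratio of 1.10. No adjusted figure was worked out for S4-S9.

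**The case against.** Collecting more candidate covariates than enter a model is ordinary, and the Baseline measurements sentence speaks of the planned analyses in general, not of one model. Strength of urges is a measure of dependence and a plausible partial proxy for intensity. The same practices are sampled in adjacent four-week periods, consecutively, on office days varied to limit sampling bias, so a large shift is not expected. Consumption is also awkward to model: cigarettes, cigarillos, pipes, cigars and hookah are all eligible and are reported per day, week or month.

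Most of this stands, and it limits the size of the point. It does not explain why two of the four named measures are missing.

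A reader might infer three stronger things that the documents do not support:

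- **That the protocol names daily/non-daily status as a confounder and then drops it.** The item is recorded in the preceding paragraph and is outside the list so described. Adding it is a suggestion; it does not repair a contradiction.
- **That a change in smoker mix passes in full into the effect.** Urges and motivation stay in the model, as do age, sex and SES, and absorb part of it.
- **That the omission costs precision.** In a logistic model, adding a prognostic covariate does not generally shrink the standard error of the log odds ratio, and no power gain has been shown.

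**Conclusion.** The mismatch is real: amount smoked and time since last cigarette are named as important for the analyses and are absent from the fixed list. The consequence is minor. Under assumed inputs (a 10-point shift in daily share and an advice odds ratio of 2 to 3), the residual spurious odds ratio for the primary outcome is about 1.03 to 1.10, or 5% to 17% of the target on the log scale. Smaller shifts give less.

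That size rests on daily status standing in for intensity and on a single proxy score, because the documents supply no figures for either. It would matter more where the true effect is small, possibly for quit attempts and abstinence, but this was not quantified for the adjusted model. S10 is largely unaffected, since a shift common to both arms mostly cancels in the interaction. This is a worthwhile refinement, not a threat to the trial's main conclusion.

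**What to change.** Before the outcome data are analysed, amend the covariate list in the section on analyses of primary and secondary outcomes, for the primary outcome and S1-S9:

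- Add baseline consumption on a pre-specified common scale, for example units per day, with weekly and monthly reports converted and a stated rule for products other than cigarettes.
- Add daily/non-daily status as a simple measure that does not depend on the product smoked.
- Say in one sentence why time since last cigarette is left out, or include it, so that the two sections agree.
- Show smoking characteristics by period as well as by arm, so that any shift in mix can be seen.

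No new data are needed. The cost is one or two extra terms, which partly overlap with strength of urges, in a sample planned at 2016 patients, plus the work of defining the conversion.

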#### Secondary outcomes

Secondary outcomes S1–3 will be collected together with the primary outcome through personal interviews immediately after GP consultation and refer to the patients’ last consultation with their GP. Data on secondary outcomes S4–9 will be collected by means of three follow-up questionnaires by postal dispatch. The denominator of all secondary outcomes is the number of patients who stated to be current tobacco smokers at the time of the consultation with their GP.S1: Number of patients who report the receipt of a recommendation for individual or group behavioural support for smoking cessation;S2: Number of patients who report the receipt of a recommendation or prescription of NRT for smoking cessation;S3: Number of patients who report the receipt of a recommendation or prescription for varenicline or bupropion for smoking cessation;S4–6: patient-reported rates of quit attempts after 4, 12, and 26 weeks following the consultation with the GP;S7–9: patient-reported point prevalence abstinence rates at 4, 12, and 26 weeks following the consultation with the GP;S10: Interaction effect between time (from pre-to post-training) and group variable (5A vs. ABC) for the primary and secondary outcomes S1-S9.

Furthermore, this study aims to assess additional data in GPs on to what extent one 3.5-h-training session according to either the 5A or the ABC method affects, at least in the very short-term (immediately following the training), self-perception of GPs’ attitude towards (motivation), knowledge on, and practical skills (capability) in the provision of brief advice to quit tobacco consumption.

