#### Follow-up measurements

Four (time window = + 1 week), 12, and 26 weeks (time windows = + 2 weeks, respectively) after consultation with their GP, patients who reported to be a tobacco smoker at baseline will receive a follow-up questionnaire (see Additional files 3 and 4) by postal dispatch. This questionnaire collects data on secondary outcome (S4-S9): whether or not patients have made an attempt to quit from baseline (GP consultation) to follow-up, and on their current smoking status (S 7-9= point prevalence abstinence rates). In relation to this, questions will be asked about what triggered that attempt (e.g., advice of GP, smoking-related disease, cigarette package health warnings), whether it was supported by evidence-based (e.g., NRT) or non-evidence-based smoking cessation treatments (e.g., acupuncture, hypnosis), and how long this attempt to stop did last (if so). In order to avoid overlaps with further consultations or multiple quit attempts which might have taken place since the initial consultation, the questions will be clearly formulated with reference to specific dates or periods. To assess changes within the health-related quality of life from consultation to follow-up, a paper-based version of the EQ-5D will be sent along with each follow-up questionnaire.

Patients will receive a small unconditional and non-financial incentive together with each follow-up, which is an evidence-based strategy to increase the response rates [43–45].

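### Recoding missing S5 and S6 answers as 'no quit attempt' contradicts attempts the same patient reported at an earlier wave

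*Protocol article*

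**What the plan says.** All references are to the protocol article.

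- **Outcome.** Under Secondary outcomes, S4-S6 are "patient-reported rates of quit attempts after 4, 12, and 26 weeks following the consultation with the GP". All three are anchored to the same consultation.
- **Item.** Under Follow-up measurements, the questionnaire asks "whether or not patients have made an attempt to quit from baseline (GP consultation) to follow-up". The same section adds that "the questions will be clearly formulated with reference to specific dates or periods".
- **Mode.** "Data on secondary outcomes S4–9 will be collected by means of three follow-up questionnaires by postal dispatch". A patient can therefore answer one wave and miss another.
- **Denominator.** "The denominator of all secondary outcomes is the number of patients who stated to be current tobacco smokers" at the consultation. Non-responders stay in.
- **Missing data.** Under Analyses of primary and secondary outcome measures: "Missing data on secondary outcomes S4-S6 will be imputed and recoded as" no quit attempt. Nothing is said about answers given at other waves.
- **Sensitivity analysis.** The complete-case analysis is described for the primary outcome: "all cases with missing data on the primary outcome will be excluded from the analysis". None is described for S4-S6.

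**The concern.** Treating a missing answer as failure is usually defended as a cautious choice about an unknown value. That defence does not apply when the value is known. If the outcome is any attempt since the consultation, a 'yes' at week 4 fixes the answer at weeks 12 and 26 whether or not the later forms come back.

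At stake are two secondary outcomes, S5 and S6: their levels, their pre-post time effects, and their part of S10 (5A versus ABC). A series labelled as attempts since the consultation could also be reported as falling between waves, which is impossible for a cumulative rate.

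**Working it through.** **Step 1: the definitions side by side.** Take a patient who reports an attempt at week 4 and returns neither later form.

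| Outcome | Value fixed by the follow-up definition | Value under the missing-data rule |
|---|---|---|
| S4 | yes | yes |
| S5 | yes (attempt already made since the consultation) | no |
| S6 | yes (same reason) | no |

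S4 has no earlier wave, so the conflict cannot arise there. S7-S9 are point-prevalence abstinence; abstinence at week 4 does not determine status at week 26, so the conflict does not arise there either.

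**Step 2: simple size.** The article gives no quit-attempt rate and no postal response rate, so there is no figure to reproduce and every rate below is assumed. Let p be the share of all smokers who report an attempt at week 4, and m the share of those same patients who do not return the 26-week form. Reported attempts lost from S6 = p × m.

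- p = 0.20, m = 0.20: 4 points, or about 40 of the 1008 smokers planned per period
- p = 0.20, m = 0.40: 8 points, about 81 of 1008
- p = 0.20, m = 0.60: 12 points, about 121 of 1008

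Here m is non-response among week-4 responders, who may well be more likely than others to reply again.

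If m is the same in both periods, the post-minus-pre difference in S6 loses m × (p_post − p_pre) through this route. The same holds between arms.

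**Step 3: all waves together.** Let c4, c12, c26 be the true cumulative rates and r4, r12, r26 the response rates, with response independent of attempts. The stated rule gives r × c at each wave. Keeping earlier reports adds:

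- monotone drop-out: S5 + (r4 − r12)c4; S6 + (r12 − r26)c12 + (r4 − r12)c4
- intermittent (independent) non-response: S5 + (1 − r12)r4·c4; S6 + (1 − r26)[r12·c12 + (1 − r12)r4·c4]

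Example with c = 15/25/35% and r = 70/55/45%:

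- S5 under the rule: 0.55 × 25 = 13.8%. Keeping earlier reports: 13.75 + 0.15 × 15 = 16.0% (monotone) or 13.75 + 0.45 × 0.70 × 15 = 18.5% (intermittent).
- S6 under the rule: 0.45 × 35 = 15.8%. Keeping earlier reports: 15.75 + 0.10 × 25 + 0.15 × 15 = 20.5% (monotone) or 15.75 + 0.55 × (13.75 + 4.725) = 25.9% (intermittent).

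The full set of assumptions was c = 10/15/20% or 15/25/35%, crossed with r = 80/70/60, 70/55/45, 60/50/40 or 80/50/40%. Across it, the patients coded against their own report number 10 to 60 per 1008 on S5 (about 1-6%) and 25 to 112 per 1008 on S6 (about 2-11%).

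**Step 4: a falling cumulative rate.** With c = 10/15/20% and r = 80/50/40%, the rule gives 0.80 × 10 = 8.0% at week 4 and 0.50 × 15 = 7.5% at week 12. Keeping earlier reports gives 10.5-11.5% at week 12. In the other seven combinations the coded rates rise while still being too low, so a rising series would not show that the problem is absent.

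**The case against.** **Derivation may be settled elsewhere.** The rule concerns missing outcome data, not unreturned forms. If S5 and S6 are cumulative, an earlier 'yes' arguably means the outcome is not missing, and derivation across waves is often left to an analysis plan. This is a fair reading of what may be intended, but the article does not say it. It states the recoding without exception and mentions no derivation across waves.

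**The questions may cover separate periods.** The sentence on specific dates or periods could mean that each form asks only about the time since the last one, and the questionnaires are not shown. Then a missing later form would not contradict an earlier 'yes'. A small doubt remains. However, the same section gives the interval as baseline to follow-up, and nothing says that it restarts at each wave. The pilot item was likewise framed as attempts since the baseline consultation.

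**Stronger readings.** A reader might infer any of the following, and the documents do not support them:

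- *That all of S4-S6, or also S7-S9, are corrupted.* Step 1 limits the contradiction to S5 and S6. The stored S4 answer is not altered.
- *That general dilution by non-response, or spurious differences from unequal postal response, are consequences of this defect.* They belong to any missing-equals-no rule, affect S4 as well, and remain after the fix for patients with no earlier report. For those patients the rule is a conventional conservative choice.
- *That nothing could reveal the problem.* A fall from S4 to S5 would be visible when the waves are compared, though it need not occur.
- *That the direction of any bias from unequal response is known.* Nothing in the article shows whether response will differ between periods or arms.

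**Conclusion.** The point holds for S5 and S6 and their S10 contrasts. The defect is a stated rule that assigns a value conflicting with the article's own outcome definition, rather than a detail left unsaid. It lowers both rates and, with equal non-response, shrinks absolute differences in them.

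The illustrative loss is 4-12 percentage points at 26 weeks, and it depends entirely on the assumed 20% attempt rate and 20-60% later non-response among those reporters. The conclusion also assumes that the later forms follow the baseline-to-follow-up definition. The primary outcome, S1-S4 and S7-S9 are unaffected by this contradiction. It should be corrected, but it does not threaten the trial's main result.

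**What to change.** Add one sentence to the missing-data rule: for S5 and S6, an attempt reported at any earlier wave counts as an attempt at every later wave, and missing answers are set to no attempt only for patients with no earlier reported attempt. Check this against the 12- and 26-week questionnaires, and state in the outcome definition that S5 and S6 run from the consultation.

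Optionally, report a complete-case sensitivity analysis for S4-S6, which would show how much these results depend on the remaining recoding.

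The cost is one sentence and one derived variable. No new data, follow-up or change in sample size is needed.

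### Postal non-replies are coded as failures for S4–S9, and the one stated sensitivity analysis does not test that coding, so a pre/post change in reply rates can create or mask an effect

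*Protocol article*

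**What the plan says.** Under Secondary outcomes, the article states: "Data on secondary outcomes S4–9 will be collected by means of three follow-up questionnaires by postal dispatch". The same section fixes who is counted: "The denominator of all secondary outcomes is the number of patients who stated to be current tobacco smokers" when they saw their GP, whether or not they later reply.

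The handling of missing values is under Analyses of primary and secondary outcome measures:

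- Analysis set: "All participating patients will be included in an intention-to-treat analysis".
- Quit attempts: "Missing data on secondary outcomes S4-S6 will be imputed and recoded as" no quit attempt.
- Abstinence: "Missing data on secondary outcomes S7-S9 will be imputed and recoded as" smoker at follow-up.
- Sensitivity: one complete-case analysis, "which means that all cases with missing data on the primary outcome will be excluded from the analysis".

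That section calls the risk of missing data small only for the interview outcomes (the primary outcome and S1–S3). S4–S9 use the primary model: a fixed pre/post time effect, random practice and time effects, and adjustment for age, sex, SES, motivation and urges. The arms are compared only through the time-by-group interaction (S10). The article gives no expected reply rate for the postal waves.

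**The concern.** The sensitivity analysis covers the outcomes where few values should be missing and passes over those where missing values are most likely. The article itself gives reason to expect them: under Study procedures it reports poor baseline data in the pilot when patients filled in the questionnaire themselves, and the main trial moved to interviews partly for that reason. S4–S9 still depend on self-completed forms sent by post.

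Coding a non-reply as failure is often regarded as cautious. For a single rate it is. For a contrast it is cautious only if replies are balanced, or if those who do not reply really are failures. The S4–S9 contrast sets patients seen before training against other patients seen after it, so randomisation does not balance their reply behaviour. Covariate adjustment allows for a different patient mix but does not undo the coding.

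At stake are the claims about quit attempts and abstinence, and the corresponding S10 comparisons.

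**Working it through.** **Inputs from the article (Power and sample size; Planned statistical analyses).** 48 practices × 21 patients per period = 1008 per period, and 2 × 1008 = 2016, which matches the stated total. Wald test at 0.05, taken as two-sided. Advice is assumed to rise from 18% to 23% (5A) or 33% (ABC). The article gives no planning figure for S4–S9 to reproduce.

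**Assumptions, because the article gives no figure.** True attempt rate 25% in both periods; replies 60% before training; clustering ignored; at first, non-repliers succeed as often as repliers.

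**Step 1: what the coding does.** With missing = failure and all baseline smokers in the denominator,

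coded rate = reply rate × success rate among repliers.

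For replies of 60% and 50%:

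- Coded rates: 0.60 × 0.25 = 0.150 and 0.50 × 0.25 = 0.125.
- Odds ratio: (0.125/0.875) / (0.150/0.850) = 0.81.
- SE of the difference: √(0.15 × 0.85/1008 + 0.125 × 0.875/1008) = 0.0153.
- z = 0.025/0.0153 = 1.63.
- Rejection probability: Φ(1.63 − 1.96) + Φ(−1.63 − 1.96) ≈ 0.37.

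**Step 2: range of reply differences, no true effect.**

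| Replies pre / post | Coded rates | False OR | Rejection (nominal 5%) |
|---|---|---|---|
| 60% / 60% | 15.0% / 15.0% | 1.00 | 5% |
| 60% / 58% | 15.0% / 14.5% | 0.96 | 6% |
| 60% / 55% | 15.0% / 13.75% | 0.90 | 13% |
| 60% / 50% | 15.0% / 12.5% | 0.81 | 37% |
| 60% / 70% | 15.0% / 17.5% | 1.20 | 33% |

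For abstinence at an assumed 5–10%, replies of 60% / 50% give 10–17% rejection, and 60% / 58% give 5.2–5.4%.

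**Step 3: masking.** A true rise from 25% to 30% with replies of 60% and 50% is coded as 0.60 × 0.25 = 15% and 0.50 × 0.30 = 15%. The effect disappears.

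**Step 4: relax the assumption about non-repliers.** Let them succeed at f times the repliers' rate, with a true overall rate of 15% in both periods and replies rising from 60% to 70%. The coded rate is 0.15 × r / (r + (1 − r)f), where r is the reply rate.

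| f | Coded pre / post | False OR |
|---|---|---|
| 0 | 15.0% / 15.0% | 1.00 |
| 0.25 | 12.86% / 13.55% | 1.06 |
| 0.5 | 11.25% / 12.35% | 1.11 |
| 1 | 9.0% / 10.5% | 1.19 |

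**Step 5: comparison of arms (S10), 504 patients per arm and period, true rate 15%.**

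- Replies constant at 60% in one arm and 50% in the other: interaction OR 1.00, rejection 5%. With a common true effect (15% to 20%) it is 0.994.
- Replies 60% to 60% in 5A and 60% to 70% in ABC: interaction OR 1.19, rejection 9%.

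**Step 6: does the stated check see this?** The complete-case set drops a patient only if the primary outcome is missing. That outcome is taken at interview straight after the consultation. A patient who was interviewed and then never replied by post has it, so remains in the set and is still counted as a failure on S4–S9.

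**The case against.** **The size.** No figure in the article supports a 10-point gap in replies. If advice itself drives replying, the planning assumptions imply only a small gap: advice rises from 18% to an average of (23 + 33)/2 = 28%, or 10 points. If being advised shifted replying by 20 points (an assumption), overall replies would move by 0.10 × 20 = 2 points, which is the 6% row. A 10-point gap would need a shift of 100 points; if only advice from trained GPs mattered, 10/0.28 ≈ 36 points. Every baseline smoker also receives the same questionnaires and the same unconditional incentive. This stands: 37% illustrates a large gap and is not a forecast.

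**Non-repliers may mostly be failures.** If so, the coding is nearly right. This also stands, but the article does not argue it, and it is harder to assume for having tried to quit than for being abstinent.

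**An analysis plan may add checks.** It may, so a reader should not infer that the trial has no sensitivity analysis for S4–S9. The point rests on what the article does fix: one coding value, and one check whose stated scope leaves that value untested.

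**Two stronger readings fail.** A reader might infer that any reply difference turns into a training effect; Step 4 shows that it need not. A reader might also infer that a reply difference between arms biases the comparison of 5A with ABC; Step 5 shows that a constant difference cancels, because the arms are compared only through the interaction.

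**Conclusion.** The point holds in limited form. The coding of postal non-reply, with a complete-case analysis defined by the primary outcome alone, leaves S4–S9 open to bias from a pre/post difference in replies. The S10 tests on these outcomes are open to it where the change in replies differs by arm. The bias can go either way.

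At a true attempt rate of 25%, false rejection is about 6%, 13% or 37% for reply gaps of 2, 5 or 10 points. These figures assume 1008 patients per period, non-repliers like repliers and no clustering. They fall towards 5% as non-repliers succeed less often. Reply and success rates are assumptions throughout.

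The primary outcome and S1–S3 come from the interview and are unaffected.

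**What to change.** Keep the stated coding as the main analysis of S4–S9 and add to the plan:

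1. A complete-case (respondents-only) analysis for each of S4–S9, defined by that outcome's own missing data.
2. A multiple-imputation sensitivity analysis using period, arm, practice, reported advice, the baseline covariates and earlier waves. It assumes that these variables explain non-reply, so it is a second view and does not settle the matter.
3. Reply rates by period, arm and wave.
4. A statement that conclusions on S4–S9, and on the matching S10 tests, will be qualified where the analyses disagree.

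The cost is some wording and modest programming, with no new data and no change in sample size. The drawback is that conclusions on these secondary outcomes may have to be more guarded.
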